### Inclusion and exclusion criteria

All villages within the five Divisional Secretariats will be eligible for study entry except those recruited to our previous pilot studies. If necessary, additional households will be recruited from Ipalogama, a neighbouring divisional secretariat, to ensure an adequate number of households are enrolled. Those households in the intervention arm where farm workers are resident and where pesticide use or storage is reported will be eligible for a lockable safe storage box. Households where there is no adult available to provide consent will be excluded.

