### Randomisation

In this cluster randomised trial, villages (or groups of adjoining villages where boundaries are blurred; see Discussion) are the randomisation unit and are allocated to either the intervention or comparison group. Large imbalances between study arms in the number of allocated villages, the number of villagers in households eligible for a box, and the previous history of pesticide self-harm in the village, are avoided by the method of minimisation. Prior to allocation the village is added to each arm in turn and the differences on the three minimisation variables calculated. The odds of randomly allocating that village to one arm rather than the other is then modified to give an improved chance of the allocation, which achieves better balance between the two arms.

Steps have been taken to avoid selection bias during random allocation: (i) Villages are only randomised once household demographic data has been collected from all villages in the study administrative band; after this has been done villages cannot be withdrawn from or added to the study; (ii) The UK-based study statistician, who does not come into contact with study villages or data collectors, uploads data on the minimisation variables to an automated computer randomisation programme. Hence allocation concealment is ensured, it neither being possible to predict allocations, nor to withdraw or recruit villages or households once the allocation is known.

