**Figure 3 F3:**
[figure not shown]
**Safe storage device for agrochemicals in Sri Lanka**. The UV-resistant plastic pesticide storage container to be used in this study. A) Device before installation: the metal bar at the base secures the device from theft. B) Device buried with two lids to protect the padlock from weather damage. C) Device can store several large and small bottles of pesticides. *Copyright [name]*.

Following randomisation the GN official (lowest level of civil administration) in the villages in the intervention arm is informed and arrangements made for distribution of the devices to eligible households. A small demonstration is given and a range of materials are utilised to ensure the box is installed and used correctly. Efforts are made to ensure that the boxes are installed in field, compound or house and members of the distribution team follow up in the village to ensure all eligible people receive a box. Where the distribution team is uncertain about the eligibility of households they are required to bury the device to reduce the likelihood of contamination. Further promotion after distribution is limited to six monthly activities of limited scale in the villages.

As an evaluation of intervention adherence, a small sub-study in approximately five villages will be undertaken to examine the use of the safe storage device. Household opinions on the usefulness of the devices will be elicited through a survey and focus groups. In addition, the demographic survey will be repeated in each village at the end of the study to better estimate person years of follow-up and to observe whether the containers are still being used.

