### Pre-specified statistical analysis plan

The primary analysis will follow the intention-to-treat principle, comparing the observed incidence of self-harm using pesticides between individuals in villages allocated to the intervention, and individuals in villages allocated to the control arm. A Poisson regression model will be employed, with the standard errors inflated to accommodate the clustered design. This analysis will be adjusted for minimisation variables used in the random allocation and for seasonal variation in the incidence of pesticide self-poisoning. This same approach will also be used for the secondary outcome measures.

Pre-specified subgroup analyses will investigate whether the effectiveness of the safe storage intervention is modified by the village-level historical rate of self-poisoning (established in the baseline survey) and proportion of households provided with a locked box. We will perform a sensitivity analysis excluding the five intervention villages where sub-studies are undertaken as their participation may increase household compliance with safe storage.

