### Sample size

Our previous research has found the incidence of self-poisoning in the district to be approximately 350 per 100,000 per year [3,5]. Fifty per cent of episodes involve pesticides - an incidence of 175 per 100,000 per year, or 525/100,000 over the three years of the study. We hypothesize that provision of pesticide storage containers might reduce the incidence of pesticide self-poisoning by 33%, from 175/100,000 to 117/100,000. At 80% power and 5% type I error rate, a total of 68,676 person years of follow-up are required in each arm of the study to detect a true intervention effect of this size.

The sample size for this study needs to be increased to allow for variation in self-harm rates between villages (i.e. the randomisation unit). Using our data on pesticide poisonings in 189 Sri Lankan villages [3], we estimate the design effect, or sample size inflation factor, to be at least 1.64. Compensating for clustering with a design effect of 1.75 (to allow for error in our estimate), 120,183 person years are required in each arm of the trial. To achieve this number of years of follow-up, for each trial arm 40,061 individuals must be followed for an average of three years.

However, some households within intervention villages will not use pesticides (and therefore not be offered a container), while others will not use their container (non-compliance). Some households within control villages may acquire a lockable container (contamination). If 20% of individuals in the intervention arm live in households not using a lockable container, and 5% of individuals in the control arm live in a household using a lockable container, then 217,944 person years of follow-up are required in each arm of the trial to compensate (24,216 households; 81 villages per arm; total 162 villages). Our assumptions about the number of households per village, the average number of household members, and the proportion of eligible households in each village, will be monitored as the baseline survey proceeds, and compensatory action (increasing the sample size) will be taken if deviations from those assumptions are likely to challenge the statistical power achieved.

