### Engaging control villages

At the end of the study, unless there is evidence that the containers are harmful, households in control villages will be offered a safe storage container. Focus groups were carried out before the study started to determine whether this offer is sufficient to encourage villages to enter the study despite the risk of being randomised to no intervention. These focus groups indicated that villagers consider that the offer of a free safe storage container, together with the great importance of pesticide poisoning to their communities, to be sufficient to encourage villages to enrol.

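### One of the two pre-specified subgroup modifiers, the share of households given a box, is zero by design in every control village, so its interaction with arm cannot be estimated; the baseline-eligible share should replace it

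*Protocol article*

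**What the plan says.** The Protocol article (Pre-specified statistical analysis plan) names two village-level effect modifiers. The first is the "village-level historical rate of self-poisoning (established in the baseline survey"). The second is the "proportion of households provided with a locked box". The reference to the baseline survey belongs to the first only.

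Three other sections determine what values the second modifier can take:

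- **Inclusion and exclusion criteria:** "Those households in the intervention arm where farm workers are resident and where pesticide use or storage is reported will be eligible" for a box.
- **Trial intervention** (text after Figure 3): "Following randomisation the GN official (lowest level of civil administration) in the villages in the intervention arm is informed", and distribution is arranged from there.
- **Engaging control villages** puts the control arm's offer of a box after follow-up: "At the end of the study, unless there is evidence that the containers are harmful, households in control villages will be offered a safe storage" …

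Elsewhere the article uses a different, baseline quantity. Minimisation (Randomisation) balances "the number of villagers in households eligible for a box", and the Sample size section says that "the proportion of eligible households in each village, will be monitored as the baseline survey proceeds".

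**The concern.** A test of effect modification asks whether the intervention effect differs between villages that differ on some characteristic. That characteristic must therefore vary in both arms and should be fixed before allocation. The share of households given a box meets neither condition: it comes into being through the allocation and has a single value, zero, in the control arm.

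Two things are at stake. First, a pre-specified analysis that cannot be run as worded will have to be replaced later, perhaps once outcomes are known, and then loses the protection of pre-specification. Second, the contrast that remains compares intervention villages with high and low provision. Provision follows how many households farm and report pesticides, mixed with how well delivery went. Pesticide availability is the trial's own proposed route to self-poisoning, so such villages could differ in underlying rate without any box.

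**Working it through.** **1. Identification (no assumed figures).** Let A be arm (1 intervention, 0 control) and P the proportion of a village's households given a box. By the sections cited above, P = 0 whenever A = 0. Hence A × P = P in every village, and

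log rate = b0 + b1·A + b2·P + b3·(A × P) = b0 + b1·A + (b2 + b3)·P.

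Only the sum b2 + b3 can be estimated. Here b2 is the prognostic slope (how the rate changes with the characteristic without a box) and b3 is the modification of interest. A numerical check with 162 villages, 81 per arm, gave rank 3 for the 4 columns.

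Now let E be the proportion of households eligible at the baseline census, which varies in both arms. Control villages estimate b2, intervention villages estimate b2 + b3, and the difference is b3. The same check gave rank 4 of 4.

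The 5% control-arm contamination in the Sample size section does not change this. Those households acquire and use a container; the trial does not provide it.

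**2. The plan's own figures.** The article gives no figure for this subgroup analysis. Its sample size is used below only as an input, and it reproduces. Three-year risks per 100,000 after dilution are 0.95 × 525 + 0.05 × 351 = 516.3 (control) and 0.8 × 351 + 0.2 × 525 = 385.8 (intervention), where 351 = 3 × 117. With design effect 1.75, 80% power and two-sided 5% (sidedness is an assumption), comparing two Poisson rates gives 218,273 person-years per arm and comparing two proportions gives 217,287. The stated figure is 217,944.

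**3. What the remaining gradient can do (assumed inputs).**

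- From the documents: 81 villages and 217,944 person-years per arm. The control rate of 172 per 100,000 per year follows from 516.3 / 3, and the true rate ratio of 0.75 from 385.8 / 516.3 = 0.747.
- Assumed: eligibility uniform from 0.50 to 0.95; every eligible intervention household gets a box; between-village standard deviation 0.35 on the log scale; **no** effect modification; no covariate adjustment.
- Method: Poisson regression with standard errors scaled for overdispersion, 500 runs per row.
- Varied: the log-slope of the underlying rate on eligibility. The second column is exp(0.45 × slope), the underlying rate ratio between villages at 0.95 and 0.50 eligibility.

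| Assumed slope | Rate ratio, 0.95 v 0.50 | Mean slope on P | P slope significant | A × E significant |
|---|---|---|---|---|
| 0 | 1.00 | -0.03 | 5% | 3% |
| 0.5 | 1.25 | 0.51 | 14% | 5% |
| 1 | 1.57 | 1.00 | 41% | 6% |
| 1.5 | 1.96 | 1.46 | 70% | 6% |
| 2 | 2.46 | 1.98 | 93% | 4% |

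The slope on P returns the assumed prognostic slope, as step 1 predicts when b3 = 0. The interaction with baseline eligibility stays near the nominal 5% in every row.

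**The case against.** The strongest defence is that the phrase is loose shorthand for the baseline-eligible share. Eligibility has to be worked out in every village before allocation, because it feeds minimisation, and "Villages are only randomised once household demographic data has been collected from all villages in the study administrative band". The Trial intervention section also aims for every eligible household to get its box, so provision is meant to approximate eligibility. This reading is plausible and may be what was intended. It does not rescue the text: the article says *eligible* in the Randomisation and Sample size sections and *provided* here, and ties only the other modifier to baseline.

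A second defence is that this is a condensed article and the model for a subgroup analysis normally sits in a fuller document. That is right about the model, and no finding is made on it. The choice of variable, however, is stated here.

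A third is adjustment. The primary model adjusts for the minimisation variables, which include past pesticide self-harm in the village. If carried into the subgroup analysis, which the article does not state, this should reduce confounding by an unknown amount. The eligibility covariate is a count of villagers, not a proportion, so it would do only part of the work, and A × P would still duplicate P.

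A reader might go further and infer that the plan will compare high- and low-provision intervention villages with all controls pooled, and so will report spurious modification. The documents do not support that. They nowhere describe such a comparison, and it is not the only workable analysis, since both arms can be classified by baseline eligibility. Nor do they give any relation between village eligibility and self-poisoning rate from which to size a bias.

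**Conclusion.** As worded, the second modifier cannot support a test of effect modification. That rests on the article's account of who gets boxes and when, and on no assumed figure. Any gradient across intervention villages by provision would be a non-randomised comparison, open to confounding by farming and pesticide intensity. How large that bias would be is unknown: the 5% to 93% range reflects the assumed slopes, eligibility range and between-village variation, and shows only that the result is governed by a quantity the documents do not give.

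The reach is limited to one secondary subgroup analysis. The primary intention-to-treat comparison, the secondary outcomes, the sample size and the other modifier are untouched. It should be fixed, but it does not threaten the trial's main conclusion.

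**What to change.** In the Pre-specified statistical analysis plan, replace the second modifier with the village-level proportion of households eligible for a box at the baseline census. State that the same eligibility criteria are applied to households in both arms, from census data and before allocation; the eligibility wording now covers the intervention arm only. Use the census classification rather than later decisions by the distribution team, which the Trial intervention section shows can be uncertain. Test arm × baseline-eligible proportion, with the main effects of both and the same adjustment as the primary model.

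If a description of outcomes by actual provision is still wanted, label it as a non-randomised comparison within the intervention arm.

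The cost is one phrase and a clarifying sentence. The census already records pesticide use for participating households in every village, eligibility is already derived for minimisation, and the proportion is already monitored for the sample size. The change should be made before outcomes are examined by arm.

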### Sample size

Our previous research has found the incidence of self-poisoning in the district to be approximately 350 per 100,000 per year [3,5]. Fifty per cent of episodes involve pesticides - an incidence of 175 per 100,000 per year, or 525/100,000 over the three years of the study. We hypothesize that provision of pesticide storage containers might reduce the incidence of pesticide self-poisoning by 33%, from 175/100,000 to 117/100,000. At 80% power and 5% type I error rate, a total of 68,676 person years of follow-up are required in each arm of the study to detect a true intervention effect of this size.

The sample size for this study needs to be increased to allow for variation in self-harm rates between villages (i.e. the randomisation unit). Using our data on pesticide poisonings in 189 Sri Lankan villages [3], we estimate the design effect, or sample size inflation factor, to be at least 1.64. Compensating for clustering with a design effect of 1.75 (to allow for error in our estimate), 120,183 person years are required in each arm of the trial. To achieve this number of years of follow-up, for each trial arm 40,061 individuals must be followed for an average of three years.

However, some households within intervention villages will not use pesticides (and therefore not be offered a container), while others will not use their container (non-compliance). Some households within control villages may acquire a lockable container (contamination). If 20% of individuals in the intervention arm live in households not using a lockable container, and 5% of individuals in the control arm live in a household using a lockable container, then 217,944 person years of follow-up are required in each arm of the trial to compensate (24,216 households; 81 villages per arm; total 162 villages). Our assumptions about the number of households per village, the average number of household members, and the proportion of eligible households in each village, will be monitored as the baseline survey proceeds, and compensatory action (increasing the sample size) will be taken if deviations from those assumptions are likely to challenge the statistical power achieved.

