**Figure 1 F1:**
[figure not shown]
**Household storage of pesticides in pilot studies in Sri Lanka**. **Left - **% of households storing pesticides safely in or around their house in the five studies. **Right - **Comparison of the % of households in Study A storing pesticides in their household (top line) and the % storing pesticides safely locked up (bottom line) after provision of a safe storage container. The hatched area represents households storing unlocked pesticides. ***Note***, there was no change in the number of households that stored pesticides in the house without locking them away. Instead, the intervention markedly increased the absolute number of households storing pesticides in the house, potentially increasing the risk of poisoning if the compliance with locking them away fell away over time.

Although in one of the studies 82% of containers were locked securely at 7 months, by 24 months this had dropped to 55% [23].In addition, the use of the lock may decline over time and households may find it difficult to keep the key hidden from younger household members. Two further studies showed similar patterns in the drop- off in compliance after 12 months [24,25]. So, before this approach is implemented more widely a large scale community trial is required to determine its effectiveness and safety [26].

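### The stated 80% power depends on a flat 20% non-use over three years, which the protocol's only data on container use do not support

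*Protocol article*

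**What the plan says.** The Sample size section starts from "an incidence of 175 per 100,000 per year, or 525/100,000 over the three years of the study" and supposes that containers "might reduce the incidence of pesticide self-poisoning by 33%, from 175/100,000 to 117/100,000". It then states: "At 80% power and 5% type I error rate, a total of 68,676 person years of follow-up are required in each arm". Next comes the cluster allowance: "Compensating for clustering with a design effect of 1.75 (to allow for error in our estimate), 120,183 person years are required" per arm.

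The last step allows for dilution. The section explains that "some households within intervention villages will not use pesticides (and therefore not be offered a container), while others will not use their container". Both groups are put into one figure: "If 20% of individuals in the intervention arm live in households not using a lockable container". With 5% of control individuals in households that use a lockable container, the requirement becomes 217,944 person-years per arm. The abstract repeats that number with 80% power. No source is given for the 20%.

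The Background gives the only data on use over time: "Although in one of the studies 82% of containers were locked securely at 7 months, by 24 months this had dropped to 55" per cent. It adds: "Two further studies showed similar patterns in the drop- off in compliance after 12 months".

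The Sample size section also promises to enlarge the trial if households per village, household size or the eligible proportion depart from what was assumed. Container use is not on that list.

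**The concern.** A flat 20% means 80% of individuals live in a household that uses its container, on average over all 36 months. In the pilot, 18% of containers were already not securely locked at month 7. Table 1 counts pilot households that had received a container and were using pesticides at 7 months, so households never offered one would add to that. A constant 20% therefore leaves about 2 percentage points for all later decline and for every ineligible household. The protocol's own case for running the trial is that locking may fall away with time.

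The power claim is what is at stake. If use declines as it did in the pilot, the trial could miss the diluted effect more often than the stated one time in five, and a null result could be read as showing that containers do not work.

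**Working it through.** **Inputs.** From Sample size: 175 and 117 per 100,000 per year, design effect 1.75 (estimated as at least 1.64), non-use 20%, contamination 5%, 217,944 person-years per arm. From Background: 82% locked at month 7, 55% at month 24.

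**Reproducing the plan's figure.** Rates per 100,000 person-years:
- Intervention: 0.80 × 117 + 0.20 × 175 = 128.6
- Control: 0.95 × 175 + 0.05 × 117 = 172.1
- Rate ratio: 128.6 / 172.1 = 0.75

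The pooled two-proportion formula (two-sided 5%, one person-year as the unit), multiplied by 1.75, gives 217,944, an exact match. The simpler form, 1.75 × (1.96 + 0.84)² × (sum of rates) / (difference)², gives about 218,300. The earlier step also holds: 68,676 × 1.75 = 120,183.

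**Mean use over 36 months.** Use is taken as linear from 82% at month 7 to 55% at month 24. That stretch averages 68.5% over 17 months, a fall of 27/17 = 1.59 points a month. Use before month 7 and after month 24 was not reported, so both are varied. If the decline continues, use at month 36 is 55 − 12 × 1.59 = 35.9%, and the last 12 months average 45.5%.
- A. 82% to month 7; 55% held after month 24: (7 × 82 + 17 × 68.5 + 12 × 55) / 36 = 66.6%
- B. 82% to month 7; decline continues: (7 × 82 + 17 × 68.5 + 12 × 45.5) / 36 = 63.4%
- C. 100% at month 0, falling to 82% at month 7; 55% held: (7 × 91 + 17 × 68.5 + 12 × 55) / 36 = 68.4%
- D. As C, with the decline continuing: 65.2%

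**Power.** Let u be mean use. Intervention rate = u × 117 + (1 − u) × 175; the control rate stays at 172.1. Standard error = √(1.75 × sum of rates / 217,944). Power = Φ(difference / standard error − 1.96).

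For A: intervention rate 136.4, difference 35.7, standard error 15.7, ratio 2.27, so power = Φ(0.31) = 62%.

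| Case | Mean use | Rate ratio | Power, design effect 1.75 | Power, design effect 1.64 |
|---|---|---|---|---|
| Plan | 80% | 0.75 | 80% | 82% |
| A | 66.6% | 0.79 | 62% | 65% |
| B | 63.4% | 0.80 | 57% | 60% |
| C | 68.4% | 0.79 | 65% | 68% |
| D | 65.2% | 0.80 | 60% | 63% |

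**Observed months only.** Averaging the first 24 months, without extrapolation:
- 82% to month 7: (7 × 82 + 17 × 68.5) / 24 = 72.4%, power 71%
- 100% at the start: (7 × 91 + 17 × 68.5) / 24 = 75.1%, power 74%

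**Ineligible households.** The document gives no eligible proportion. If 90% of individuals were in eligible households (an assumption), multiplying u by 0.9 gives 48-55% for cases A to D at design effect 1.75. This also assumes that ineligible households carry the same risk as the rest.

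**Person-years for 80% power.** For cases A to D, the pooled formula at design effect 1.75 requires 312,015 (C) to 370,276 (B) per arm.

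**The case against.** A reader might infer that the pilot contradicts the 20% and that the trial has 57-62% power or less. The documents do not support that, for these reasons.

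- **The devices differ.** Table 1 lists in-house wood and metal containers for the pilot with 24 months of follow-up. The Trial intervention section describes a redesigned two-lid plastic container, developed partly because pilot locks were damaged or corroded. The trial also provides demonstrations, an installation audit within two months and help with installation. Use may hold up better. The protocol does not, however, state an expected long-term use rate, and the Background expects lock use to decline for reasons beyond hardware.
- **Locked is not the same as used.** The pilot figure is the share of containers locked; the plan's is the share of individuals in households using one. The denominator at 24 months is not stated. Treating the two as equal is an approximation, though no other measure is available.
- **The other pilots add little.** Table 1 gives the two further pilots 18 and 7 months of follow-up. The one with 7 months cannot show a drop-off after month 12, so the text and the table need reconciling. The 55% rests on one pilot.
- **Eligibility is already monitored.** The plan would enlarge the sample if the eligible proportion falls short. If ineligible households contributed no cases while the overall rate stayed at 175, they would cause no dilution.
- **This is an effectiveness trial, and the 20% is stated conditionally.** Dilution by real non-use is part of the question, and the intention-to-treat estimate stays valid. That protects the estimate but does not support the stated power.

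All these points limit how firmly a replacement figure can be given. None supplies support for 20% as a three-year average.

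**Conclusion.** The point holds as a statement about support: the 80% power rests on an input that the document does not justify and that its only use data do not bear out beyond the early months. The 82% at 7 months agrees with the assumption; the later decline does not.

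Power is about 57-65% at design effect 1.75, or 60-68% at 1.64, on four conditions: the redesigned container follows the one pilot's decline, locking stands for use, non-users gain nothing (as the plan's own dilution assumes), and every household is eligible. The most favourable reading, the observed 24 months alone, gives 71-74% at design effect 1.75. These are scenarios, not the trial's known power. The 48-55% at 90% eligibility is more conditional still and should not be quoted without its two assumptions.

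A reader might also infer that the analysis is deficient without a term for time since distribution. That does not follow: such a term is a secondary matter that an analysis plan not shown here may contain.

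**What to change.** In the Sample size section, and in the abstract where the power is repeated:

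1. Either justify 20% as a three-year average for the redesigned container, or replace it with the eligible proportion from the baseline census multiplied by expected mean three-year use.
2. Restate power and the detectable arm-level rate ratio as a range over plausible use, giving the assumptions about early and late use.
3. Add container use to the assumptions that are monitored.
4. In the Background, reconcile the statement about the two further pilots with their follow-up in Table 1.

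An arm-by-year-since-distribution term may be added as a secondary analysis; it is optional.

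The cost is a recalculation and some rewording. No extra enrolment is needed for this correction. The downside is a less favourable stated power.
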